EUC consists of SDOH screening, referrals to food pantries, assistance enrolling in food programs (e.g., SNAP), and access to CDC-approved HTN Self-Management Education Series (SMES) and, if applicable, DM2 SMES. *In addition to the EUC offerings*, participants randomized to FoRKS will receive home-delivered ingredient kits and Webex cooking classes with embedded lessons in kitchen organization, tool use, nutrition, budgeting, and shopping.

Specific Aims and Hypotheses:

1. **Primary Aim.** Determine the effects of FoRKS on disease management.

Effectiveness Hypothesis: Compared to EUC at PT, FoRKS participants will have lower mean systolic blood pressure (SPB) (-5.0 mm Hg). Among those with both DM2, we will secondarily examine FoRKS’ effect in lowering HbA_1c_.

1. **Intervention Processes**. Identify behavior change levers and their associations with change in food security, nutrition, and SBP.

Intervention Process Hypotheses: 2.1) FoRKS participants will report greater food-related social support and self-efficacy, and food management skills at PT and 2.2) these gains will partially account for better food security, nutrition, and SBP relative to EUC. 2.3) Higher learning engagement will be associated with greater social support, self-efficacy, and food skill gains among FoRKS participants.

1. **Maintenance.** From PT to FU, determine the percent of FoRKS versus EUC participants who maintain improved food security, nutrition, and SPB (and/or HbA_1c_ if applicable).
2. **Reach and Cost.** Assess reach and intervention cost-effectiveness in preliminary economic analyses.
3. **Eligibility Criteria**

The target population is midlife adults aged 35-75 years with normal cognition, food insecurity, and a recent systolic BP ≥120 mm Hg.

We will enroll only one individual per household.

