**Social Support, Food-Related Self-Efficacy and Food Resource Management (BL, PT, and FU).** Social support is a multi-dimensional construct that refers to social relationships that promote well-being through emotional, informational, and/or instrumental channels. We will use the Social Support and Eating Habits Survey. This 10-item scale captures friend and family support or sabotage of healthy food habits.

Food-related self-efficacy will be assessed by a 9-item questionnaire capturing basic cooking self-efficacy, meal preparation, and meal planning. This scale has been shown to have good test-retest reliability (range 0.46 to 0.91) and high internal consistency (coefficient alpha 0.84 to 0.86) and to capture change over time in response to cooking lessons.

Food resource management will be assessed using the Plan, Shop, Save, & Cook checklist available on the USDA SNAP-Ed Toolkit site. This 6-item scale includes 5 response options from never to always and contains items such as “how often do you plan meals ahead of time?”, “how often do you compare unit prices before buying food?”, and “how often do you shop with a grocery list?”.

**Food Security, SNAP Usage, Nutrition Literacy, and Diet Quality (BL, PT, and FU).** At all assessments, food security will be assessed with the Four Domain Food Insecurity Scale (4D-FIS). The 4D-FIS items cover shortage of food, unsuitability of food and diet, preoccupation or uncertainty in access to enough food, and lack of control over food situation. The 4D-FIS aligns conceptually with the HFSSM but has more items that yield high factor loadings on the four domains and good internal consistency (Cronbach alphas 0.69 to 0.90).

Health literacy will be tested at BL and PT with the New Vital Sign (NVS). Notably, the NVS involves math word problems that reference an ice cream nutrition label (e.g., if you were allowed 60 grams of carbohydrate as a snack, how much ice cream could you have?).

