**Intervention Measures:**

**Engagement** is “the act of being occupied or involved with an external stimulus” and will be assessed in two ways: (1) Participation: Total number of sessions attended; longest streak of consecutive classes attended, per person. This will be recorded for both EUC and FoRKS participants throughout their scheduled intervention. (2) Self-report survey: Total scores on a modified Classroom Engagement Survey, administered approximately every 3 weeks to FoRKS participants during Extended Delivery Training. This structured questionnaire has 16 items that assess, over the prior 3 weeks, the participant’s: affective engagement (e.g., “I feel interested”); behavioral engagement (e.g., “I actively participate in class discussions”); cognitive engagement (e.g., “I go back over things that I don’t understand”); and disengagement (e.g., “I let my mind wander”).

**Participant Experience** will be assessed approximately every 3 weeks to FoRKS participants during Extended Delivery Training and include Likert scale questions regarding satisfaction with foods, class content, instructions, and technology. We will summarize Likert scale scores and use qualitative feedback to make intervention adjustments as the study progresses. Once, at the PT visit, subjects will be asked about any personal “costs” experienced during the FoRKS intervention.

1. **Statistical Considerations**

**Power and Sample Size.** We determined the sample size to ensure adequate power for testing the primary hypothesis on the effectiveness of the proposed FoRKS intervention on systolic blood pressure (SBP). Specifically, we hypothesize that in comparison to EUC, FoRKS participants will have lower SBP (-6.0 mm Hg) at PT. That a difference of 6 mm Hg is clinically meaningful is supported by a 2021 Lancet meta-analysis involving 48 randomized trials and 344,716 participants that showed a reduction of >5 mm Hg in SBP was associated with a 10% reduction in major CVD events regardless of baseline SBP.

To ensure we have adequate power to detect an effect on SBP, we plan to enroll 100 subjects for each treatment group (n=80 per group at PT assuming 20% attrition). Using a conservative estimate of the SD of 12 mm Hg, we estimate that 100 subjects per group (80 after attrition) will give us 88% power to detect a 6 mm Hg difference in SBP between the treatment groups, with a two-sided t-test at 0.05 significance level.

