**Intervention Processes**. We will examine behavior change levers that are associated with food security, nutrition, and SBP. While parts of the analyses are exploratory, we are interested in testing hypotheses (H2.1 and H2.2) that FoRKS participants will report greater food-related social support and self-efficacy and food management skills at PT, and these gains will partially account for better food security, nutrition, and SBP in FoRKS participants relative to EUC. To analyze, we will first perform direct comparisons by using t-tests, but also regression analysis using mixed effect models. Specifically, we will enter repeatedly measured food security, nutrition, and SBP as dependent variables in the mixed effect models, and test the effects of food-related social support and self-efficacy, and food management skills. Similarly, to evaluate the hypothesis (H2.3) that FoRKS participants showing greater learning engagement also experience greater social support, self-efficacy, and food management skill gains, we will use regression models to examine the association between learning engagement and social support, self-efficacy, and skill gains in FoRKS participants. Finally, we will explore whether SNAP participation modified intervention effects on food security, nutrition, or SBP.

**Maintenance.** From PT to FU, we will determine and report the percent of FoRKS vs EUC participants who maintain improved food security, nutrition, SBP, and/or HbA_1c_. We will dichotomize changes in these outcomes (maintained/improved outcome vs worsened outcome) between PT and FU. We will report the percentages of maintenance and improvement in each of the outcomes. We will also conduct logistic regression analyses to model the dichotomized outcomes and identify factors associated with improvement in each of the outcomes.

**Cost-Effectiveness.** Finally, in this NIH Stage III behavioral trial, we will provide an initial indication of the cost-effectiveness of FoRKS intervention. We regard this as initial because the sample size is unlikely to provide adequate power for the cost effectiveness analysis (CEA) and we do not expect significant differences in health care use over just 24 weeks. The CEA shall adhere to the best practices of the Consolidated Health Economic Evaluation Reporting Standards.

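### H2.2 says process gains partly account for the FoRKS-EUC difference, but no step in the stated analysis estimates how much of the arm effect they account for

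*Protocol*

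**What the plan says.** Protocol section 1 (Rationale & Objectives, Intervention Process Hypotheses) states H2.1, that FoRKS raises the process measures by PT, and H2.2, that "these gains will partially account for better food security, nutrition, and SBP relative to EUC".

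Section 6 (Statistical Considerations, Intervention Processes) treats both as hypotheses under test: "While parts of the analyses are exploratory, we are interested in testing hypotheses (H2.1 and H2.2"). It gives two steps: "we will first perform direct comparisons by using t-tests, but also regression analysis using mixed effect models". The models are then specified, the analysts being required to "enter repeatedly measured food security, nutrition, and SBP as dependent variables in the mixed effect models, and test the effects of food-related social support"; the other two process measures are tested in the same way.

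Section 5 (Measures and Outcomes) schedules the process measures at the same main visits as the outcomes: "Social Support, Food-Related Self-Efficacy and Food Resource Management (BL, PT, and FU"). BP is also taken after the SMES classes, but no process measure is taken then.

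**The concern.** To say that gains partly account for a between-arm difference is to say that some share of the arm effect passes through those gains. Testing that needs an estimate of the share: an indirect effect, or the arm effect before and after adjustment for the process measure. The coefficient of a process measure in a model of the outcome is neither.

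That coefficient can also mislead. FoRKS is expected to move the process measures (H2.1) and to lower SBP (Primary Aim). When one treatment moves two variables, they become correlated across the pooled sample even if neither acts on the other. If arm is not in the model, the process measure picks up part of the arm effect. The trial could then credit a behaviour change lever that does nothing to SBP, and later versions of the intervention could be built on it.

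**Working it through.** **Hypothesis against method.** H2.2 has three components, and the plan treats them as follows.

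- Arm to process measure: supplied by the t-tests.
- Arm to outcome: supplied by the t-tests.
- Process measure to outcome, with arm held fixed: the mixed models give a process-measure coefficient, but arm is not stated to be held fixed.
- A step combining these into the part of the arm effect accounted for: none stated.

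**Inputs from the protocol.** From Power and Sample Size in section 6: 80 per arm at PT, SD 12 mm Hg, two-sided 0.05, and "FoRKS participants will have lower SBP (-6.0 mm Hg) at PT". The standardised arm effect on SBP is 6/12 = 0.5. (Section 1 gives 5.0 mm Hg. I use 6.0 because it is the figure paired with the SD; a smaller effect would lower the rates below.) The stated 88% power of the primary t-test reproduces: 88.5% by the normal formula and 88.2% by the noncentral t. No figure is stated for H2.2.

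**Assumed, because the protocol gives no value.** The arm shifts the process measure M by d = 0 to 1.0 SD; within-person correlation is 0.5 over BL, PT and FU; M has no effect on SBP.

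**Single visit (PT), no arm term.** In SD units, M = d·arm + e1 and SBP = 0.5·arm + e2 (sign ignored), with e1 and e2 independent. With 1:1 allocation arm has variance 0.25, so

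r = 0.25 × 0.5 × d / √[(1 + d²/4)(1 + 0.25/4)], and λ = r√160 / √(1 − r²).

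For d = 0.5: r = 0.0625/1.0625 = 0.0588 and λ = 0.745. The rejection rate is about Φ(0.745 − 1.96) + Φ(−0.745 − 1.96) = 0.112 + 0.003 = 11.6%. Simulation gives 11.5%. At d = 0.8 and 1.0 simulation gives 21.2% and 28.4%. With arm in the model the three rates are 5.6%, 5.8% and 5.2%.

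**Repeated measures (BL, PT, FU; random intercept), closer to the stated plan.** Share of trials in which M is falsely significant:

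| Arm effect on M (SD) | time + M | plus arm | plus arm and arm-by-time |
|---|---|---|---|
| 0 | 4.4% | 4.5% | 4.5% |
| 0.3 | 8.8% | 6.9% | 4.9% |
| 0.5 | 14.3% | 9.8% | 6.1% |
| 0.8 | 25.7% | 14.5% | 5.0% |
| 1.0 | 38.6% | 19.6% | 5.0% |

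A separate simulation gave about 8%, 15%, 29% and 39% in the first column for 0.3 to 1.0 SD, and about 6% to 21% in the second. An arm main effect alone is not enough because the arms do not differ at BL and do differ afterwards.

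**Does a significant arm-to-process t-test protect?** Not at these shifts. Requiring it as well as a significant M coefficient at PT gives false support in 10.8%, 21.2% and 28.4% of trials at 0.5, 0.8 and 1.0 SD without arm, against 5.0%, 5.8% and 5.2% with arm.

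**What the arm term does not cure.** Process measures are not randomised. With an unmeasured common cause giving M and SBP a correlation of 0.2, and d = 0.5, joint false support at PT is 79% without arm and 63% with arm.

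**The case against.** The strongest reply is that the text never says arm is left out, and its context leans towards inclusion. The Primary Aim paragraph uses mixed models of repeated BP to follow intervention effects over time, which needs arm and time. The Intervention Processes paragraph also plans to ask whether SNAP participation changes the intervention effect on the same outcomes, which needs arm too. Covariate lists and estimators for a secondary aim often sit in the SAP, which is not at hand. In addition, the aim speaks of associations and the section calls parts of the work exploratory.

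Much of this stands. A reader might infer that the process models omit arm, or that Aim 2 will report false levers. The protocol supports neither: the false-positive rates are conditional on arm being absent and on an assumed shift in the process measure, and they fall to nominal when that shift is zero. Nor is it right that the plan contains only outcome-on-process regressions, since the t-tests supply two of the components.

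What does not fall away is the mismatch. The section does not leave the H2.2 method open. It names H2.2 as a hypothesis to be tested and specifies the models and the terms to be tested, and no stated step yields the part of the arm effect accounted for. Adding arm would repair the coefficient but would not by itself supply that estimate.

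**Conclusion.** The point holds as a mismatch between a stated hypothesis and its stated analysis. As written, the plan returns separate arm comparisons and process-measure coefficients, and H2.2 can be answered by neither.

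The size of the second risk depends on a choice the protocol leaves unstated. Without arm, about 8% to 39% of trials would flag a process measure that has no effect on SBP, for assumed shifts of 0.3 to 1.0 SD and a within-person correlation of 0.5. With an arm main effect only, the figure is about 6% to 21%; with arm and arm-by-time, about 5%. These rates apply to one process measure with SBP as the outcome and assume no other common cause.

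A reader might extend the point to the trial's main result. The documents do not support that: the primary SBP t-test and its power do not use these models. This is a correction that should be made to a secondary aim.

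**What to change.** In section 6, Intervention Processes:

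- Include arm and arm-by-time in the mixed models for H2.2. Alternatively, analyse PT with arm, the baseline process measure and the baseline outcome as covariates.
- For each process measure, report the indirect effect, or the change in the arm effect with and without that measure, with a confidence interval.
- State that confounding between process measure and outcome remains possible, and add a sensitivity analysis for it.

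If the team wants association only, reword H2.2 in sections 1 and 6 to say so and keep the present models for that purpose. A lagged analysis at FU and a proportion mediated are optional and not needed to close the gap.

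The cost is a little analysis work and wider intervals than the simple coefficients give. The BL and PT data it needs are already scheduled.

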We have not determined the target sample size based on the analytical power for the secondary outcome (HbA_1c_), because we cannot control how many subjects in our sample will have both HTN and DM2.

**Data management.** Assessment data will be directly entered into REDCap, a web-based secure relational data management system for research data. A data dictionary including each interview question and definition for each response will be generated and used to build the REDCap database. The database will include internal error checking algorithms to prevent erroneous data entry or missing data. EMR and biomarker data will be merged with other study data and stored as SAS data sets on secure servers with access limited to data analysts working on this study and those meeting requirements for data sharing (see Data Storage and Sharing document). Video data will be stored using IU’s enterprise instance of OneDrive, in a HIPAA compliant secure folder created by IU for sensitive data.

**Analytic Plan**. The primary analyses will be carried out following an intention-to-treat (ITT) principle. Per-protocol analyses will be performed secondarily as supplements to the ITT analyses.

**Primary Aim.** We will use the trial data to determine the effects of FoRKS intervention on SBP and, secondarily, glucose management. We will test the hypothesis that compared to EUC, FoRKS participants have lower mean SBP at PT. Among those with both HTN and DM2, we will secondarily examine FoRKS’ effect in lowering HbA_1c_. Mean SBP at PT will be compared between the two treatment groups using a t-test. Mean HbA_1c_ will be compared using the same test. A similar analysis will be performed at FU to determine the sustainability of intervention effects on both outcomes. The planned t-tests at the end of the intervention (PT) are to evaluate the effects of the full dose of the intervention and the sustainability of the intervention at FU. This said, in addition to the main analysis described above, we will use mixed-effect models to assess the time course of the intervention effects by modeling repeatedly measured BP (BL, 5wk, PT, and FU) and HbA_1c_ (BL, PT, FU); random subject effects will be included to account for the potential correlation among repeated measures contributed by the same subjects. These secondary analyses will allow us to control the effects of any participant characteristics that are not balanced.

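### The Maintenance factor analysis models only a two-class version of the PT-to-FU change; a continuous model would gain power for SBP at almost no cost (minor)

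*Protocol*

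**What the plan says.** Section 6, Maintenance, promises the percentage of participants in each arm "who maintain improved food security, nutrition, SBP, and/or HbA_1c". It then fixes the variable: "We will dichotomize changes in these outcomes (maintained/improved outcome vs worsened outcome) between PT and FU". The percentages are reported, and the factor analysis follows: "We will also conduct logistic regression analyses to model the dichotomized outcomes and identify factors associated with improvement in each of the outcomes". No continuous model of the PT-to-FU change is named for that purpose.

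Elsewhere in section 6 the same outcomes stay continuous, but for other questions:

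- **Primary Aim.** SBP and HbA1c are compared between arms by t-test at PT, and "A similar analysis will be performed at FU to determine the sustainability of intervention effects on both outcomes". Mixed models describe the time course of BP and HbA1c.
- **Intervention Processes.** Mixed models take repeated food security, nutrition and SBP as dependent variables and test social support, self-efficacy and food management skills.

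The Maintenance aim in section 1 asks for a percentage in each arm and does not mention a model.

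**The concern.** SBP and HbA1c are continuous, the ASA-24 yields nutrient intakes, and the 4D-FIS is a multi-item scale. Keeping only the direction of change makes a rise of 1 mm Hg and a rise of 25 mm Hg the same result. The protocol cites no clinical threshold for the cut.

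The analysis asks which factors go with keeping gains once classes and deliveries stop. It has at most about 160 participants if attrition at FU is no worse than planned for PT, and fewer for HbA1c if that outcome is confined to participants with DM2. If the change scores are close to normal, the cut discards information that a linear model of the same data would use. The odds ratios also do not say how many mm Hg or score points are lost.

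**Working it through.** **Inputs from the protocol** (section 6, Power and Sample Size)

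- SD: "Using a conservative estimate of the SD of 12 mm Hg".
- Sample: "n=80 per group at PT assuming 20% attrition".
- Test: "with a two-sided t-test at 0.05 significance level".

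**Assumptions, because the protocol gives no figure**

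- PT-FU correlation ρ of 0.5, varied from 0.3 to 0.7.
- A normal change score.
- A two-level factor with 80 participants at each level.
- An even overall split at the cut.
- No further attrition between PT and FU.

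**Step 1: the plan's own figure.** The protocol claims "88% power to detect a 6 mm Hg difference in SBP between the treatment groups". The standard error is 12 × √(2/80) = 1.897, and 6/1.897 − 1.960 = 1.202, so power is Φ(1.202) = 88.5%. The noncentral t gives 88.2%. The stated 88% reproduces.

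**Step 2: SD of the change.** SD × √(2(1 − ρ)) = 12 × √(2 × 0.5) = 12 mm Hg at ρ = 0.5.

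**Step 3: the two analyses of one change score.** For a factor worth δ mm Hg in PT-to-FU change, put d = δ/12.

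- Continuous: power = Φ(d/√(2/80) − 1.960).
- Cut in two: p1 = Φ(d/2), p2 = Φ(−d/2), and power = Φ((p1 − p2 − 1.960 × se0)/se1). Here se0 is the pooled and se1 the unpooled standard error of the difference.

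For δ = 6: d = 0.5, p1 = 0.5987, p2 = 0.4013, se0 = 0.0791 and se1 = 0.0775. Then (0.1974 − 0.1549)/0.0775 = 0.548, so power is 70.8%.

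| Factor effect (mm Hg) | Continuous | Cut in two | Loss (points) |
|---|---|---|---|
| 2 | 18.3% | 13.1% | 5.2 |
| 3 | 35.2% | 24.0% | 11.2 |
| 4 | 55.9% | 38.7% | 17.2 |
| 5 | 75.0% | 55.1% | 19.9 |
| 6 | 88.5% | 70.8% | 17.7 |

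Simulation with a Wald logistic test agrees: 88% against 70% at d = 0.5, and 80% against 61% at d = 0.446. The reason is that a median cut of a normal variable has asymptotic efficiency 2/π = 0.64.

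**Step 4: sensitivity to the correlation** (same formulas)

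| ρ | Change SD | 3 mm Hg | 5 mm Hg | 6 mm Hg |
|---|---|---|---|---|
| 0.3 | 14.2 | 26.6% vs 18.4% | 60.5% vs 42.3% | 76.2% vs 56.3% |
| 0.5 | 12.0 | 35.2% vs 24.0% | 75.0% vs 55.1% | 88.5% vs 70.8% |
| 0.6 | 10.7 | 42.4% vs 28.9% | 83.8% vs 64.7% | 94.2% vs 80.1% |
| 0.7 | 9.3 | 53.2% vs 36.6% | 92.5% vs 77.0% | 98.3% vs 90.0% |

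A 70/30 split costs more than an even one. At ρ = 0.5 and 6 mm Hg the cut analysis has 66.1% power, a loss of 22.4 points. With 64 or 70 per level, the loss at a given continuous power is almost unchanged.

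**Step 5: sensitivity to the distribution.** Simulation with 80 per level, d = 0.446 in SD units and the cut midway between the group means:

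| Change score | Linear | Logistic |
|---|---|---|
| Normal | 80% | 61% |
| t, 5 df | 80% | 78% |
| t, 3 df | 83% | 94% |
| Laplace | 80% | 93% |

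The loss depends on near-normality. With heavy tails it vanishes or reverses.

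**The case against.** **The choice follows the aim.** The aim is the percentage who maintain, and logistic regression models that endpoint; mean change is a different question. This stands in part. It justifies the percentages and a supportive logistic model, but it does not require the only factor analysis to use the cut variable.

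**Continuous factor models are already planned.** This also stands in part. The Intervention Processes mixed models cover food security, nutrition and SBP, all scheduled at BL, PT and FU, so a reader should not conclude that the protocol leaves these outcomes without continuous factor models. Those models do not isolate the change from PT to FU, however, and they omit HbA1c.

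**The effect size is borrowed.** The 6 mm Hg is the planned difference between arms at PT. Nothing in the protocol says a factor moves the PT-to-FU change by that much. This stands, which is why the smaller effects are shown. At 2 to 3 mm Hg both models are weak and the difference between them is modest.

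**The loss need not apply to every outcome.** A reader might infer a flat loss of about 20 points for all four outcomes. The documents do not support that. They give no distribution for any change score, and step 5 shows that even the direction depends on the tails. Nutrition, for instance, rests on two dietary recalls per visit, and nothing shows that changes in it are normal.

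**Real factors would still often be found.** A reader might also infer that real factors will probably be missed. At 6 mm Hg and ρ = 0.5 the logistic model still has 70.8% power, so such a factor would be found more often than not.

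**An SAP may say more.** It may add a continuous model. The protocol does not leave the matter open, though: it fixes both the cut and the model.

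**Conclusion.** The point holds as a minor, cheap improvement. The Maintenance factor analysis uses only a two-class change, and the aim does not require that. For SBP, the cost is about 18 to 20 points of power for a factor worth 5 to 6 mm Hg, and about 5 to 11 points for one worth 2 to 3 mm Hg. These figures rest on a roughly normal change score, a balanced two-level factor with 80 per level, an even split at the cut, and a change SD of 12 mm Hg from an assumed correlation of 0.5. For HbA1c, nutrition and the 4D-FIS the size of the loss is not established. The primary SBP test, the arm comparisons of SBP and HbA1c at FU, and the reported percentages are all unaffected.

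**What to change.** Keep the percentages by arm as the report for the Maintenance aim. Replace the sentence on logistic regression with:

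> Factors associated with maintenance will be identified by linear regression of the continuous FU value adjusted for the PT value, with treatment arm and the stratification factors (omitting DM2 status where the analysis is restricted to DM2), for SBP, HbA1c, 4D-FIS and the nutrition measures from ASA-24, with a transformation or robust method if the residuals are markedly non-normal; logistic regression on the dichotomised outcome will be supportive.

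Three details matter:

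- Adjusting for the PT value, and not modelling the raw change alone, allows for participants whose PT reading was high or low by chance.
- DM2 status is constant within the DM2 subset and cannot be a covariate there.
- The protocol defines no single diet quality score, so the wording refers to the ASA-24 nutrition measures.

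The cost is one sentence, with no new data, visits or participants. The small downside is that the main factor results become mean differences and not odds ratios for the reported percentages; the supportive model still gives those.
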